#### Immunogenicity data:

Immunological data for each time point will be analyzed separately.

- a) Descriptive statistics (minimum, maximum, median, geometric mean, arithmetic mean and quartiles) will be computed for each immunological measure and each time point, separately for each group.
- b) For each volunteer, the ratio of the immunological measure to that assessed at baseline (during screening) will be computed. Descriptive statistics for these ratios (minimum, maximum, median, geometric mean, and quartiles) will be computed for each immunological measure and each time point, separately for each group.
- c) Wilcoxon tests will be used to compare the immunological measures between doses, and between group E and groups C or D (as appropriate) for each immunological measure, each time point and each antigen.

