## 3 Study Design

This prospective phase I, single centre, randomized, single blind, placebo controlled, dose escalating study will be conducted in 46 healthy adult volunteers. Eligible study participants will be randomized into six groups: PEV 301 10 µg (group A, n = 8) or PEV 302 10 µg (group B, n = 8) or PEV 301 50 µg (group C, n = 8) or PEV 302 50 µg (group D n = 8) or PEV 301 50 µg plus PEV 302 50 µg (group E, n = 8) or virosomes alone (group F, n = 6).

Study participants will be vaccinated three times, i.e. at days 1, 64(+2) and 183(+2) and followed-up 3 times after each vaccination. If any of the study groups does not show any immune response 3 weeks after the 2nd vaccination, no 3rd vaccination will be given to that group, i.e. the study for that group will be terminated 3 weeks after the 2nd vaccination.

Groups C & D (PEV 301 50 µg; PEV 302 50 µg) will be started 5 weeks after the 1st vaccination of groups A, B.

Group E (PEV 301 plus PEV 302) will be started 5 weeks after the 2nd vaccination of groups C and D.

Group F will be distributed and serve as a control in all groups receiving the active product.

The total duration of the study for each participant is 31 weeks, the number of visits is 13.

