## 6.3 Treatment allocation and randomization

Randomization will be computer generated. The investigator will receive envelopes with numbers (1 to 46) corresponding to the sequence of assignment to the study. In the envelope the assignment to the study group will be determined.

The 18 volunteers recruited in October will first be stratified into males and females and then randomized in blocks of 9 (1 block = females, 1 block = males) into 3 groups: Group A (n = 8) will be vaccinated with 10 µg PEV 301, Group B (n = 8) will be vaccinated with 10µg PEV 302, and 2 volunteers will receive virosomes alone (Group F). If it is not possible to have an equal sex distribution, the blocks can be filled with participants of either sex.

5 weeks later again 18 volunteers have to be recruited, they first will be stratified into males and females and then randomized into 3 groups: group C (n = 8) will be vaccinated with 50 µg PEV 301, group D (n = 8) with 50 µg PEV 302, and 2 volunteers will receive virosomes alone (Group F).

5 weeks after the 2nd vaccination of groups C and D 10 volunteers will be randomized in blocks of 5 to either group E (n = 8) receiving the combination of 50 µg PEV 301 plus 50 µg PEV 302 or group F (n = 2) receiving virosomes alone.

| Time          | N  | Dose       | PEV 301 | PEV 302 | PEV 301+302 | virosomes |
|---------------|----|------------|---------|---------|-------------|-----------|
| November 2003 | 18 | 10 µg      | 8       | 8       |             | 2         |
| December 2003 | 18 | 50 µg      | 8       | 8       |             | 2         |
| March 2004    | 10 | 50 + 50 µg |         |         | 8           | 2         |

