### 10.4 Statistical hypothesis

PEV 301 and PEV 302 are safe for inoculation into non-immune subjects. No serious adverse events attributable to either vaccine occur in the study population. One or both of the vaccines induce specific immune responses in at least 1/3 of the volunteers.

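### Every immunogenicity test in Section 10.6 compares separately randomised cohorts and none uses control group F, so the planned tests cannot show from a randomised contrast that either component induces a response

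*Protocol*

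**What the plan says.** Section 10.6, Immunogenicity data, item c (repeated in the Synopsis) gives the only immunogenicity tests: "Wilcoxon tests will be used to compare the immunological measures between doses, and between group E and groups C or D (as appropriate", for each measure, time point and antigen. In group terms these are A-C and B-D for dose, and E-C and E-D for the combination.

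Item b of the same section forms a ratio to the screening value for each volunteer and assigns it description only: "Descriptive statistics for these ratios (minimum, maximum, median, geometric mean, and quartiles) will be computed".

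Section 3 gives the control its role: "Group F will be distributed and serve as a control in all groups receiving the active product". It also says "Eligible study participants will be randomized into six groups". Section 6.3 describes something different. The first 18 volunteers are allocated among A, B and F. Then "5 weeks later again 18 volunteers have to be recruited", and these are allocated among C, D and F. The last 10 are allocated between E and F, 5 weeks after the second vaccination of C and D.

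Section 10.4 states the immunogenicity hypothesis without a comparator: "One or both of the vaccines induce specific immune responses in at least 1/3 of the volunteers".

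**The concern.** Group F receives the same virosomes without antigen (Section 6.2). It is therefore the natural reference for separating an antigen-specific response from carrier or background effects. The protocol lists its immunogenicity contrasts, and that list leaves the control out.

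The contrasts it does list are between groups that were never randomised against each other. Dose, and combination versus single component, coincide with cohort and so with calendar time. Anything else that differs between cohorts would appear as a dose or combination effect.

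At stake is the secondary objective, the immune response to each component alone and combined, and the proof of concept that the Synopsis gives as the study's aim. As written, neither is supported by a test on a randomised contrast. For cellular responses the gap is wider. Groups A and B are not assessed, so no dose test exists there, and the only test left is E versus C or D.

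**Working it through.** **Design (Sections 3 and 6.3).**

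| Cohort | Start | Active groups | F | Total |
|---|---|---|---|---|
| 1 | November 2003 | A 8, B 8 | 2 | 18 |
| 2 | December 2003 | C 8, D 8 | 2 | 18 |
| 3 | March 2004 | E 8 | 2 | 10 |

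The stated total is reproduced: 5 × 8 + 6 = 46 and 18 + 18 + 10 = 46. The protocol gives no alpha, effect size or SD for immunogenicity, so there is no power figure to reproduce.

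**Planned contrasts against this layout.** A-C and B-D compare cohort 1 with cohort 2. E-C and E-D compare cohort 3 with cohort 2. Four of four cross cohorts, and none includes F.

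**Assumptions for the simulations.** Normal values on the log scale, two-sided exact Wilcoxon test at 0.05, 20,000 runs, shifts in SD units. All are assumed.

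**Can the dose test (8 v 8) detect induction?** If both doses raise titres by 3 SD, it rejects 4.9% of the time. If neither does, it rejects 5.0%. It carries no information on whether a response exists.

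**What does a cohort shift do when dose has no effect?**

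| Between-cohort shift (assumed) | Dose test rejects |
|---|---|
| 0 | 4.8% |
| 0.25 SD | 7.6% |
| 0.5 SD | 15% |
| 1.0 SD | 44% |

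**What could the unused randomised contrasts deliver?** The smallest two-sided exact p is 2/C(n1+n2, n1).

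| Contrast | Smallest p | Power at 1 / 2 / 3 SD |
|---|---|---|
| Active v own-cohort F, 8 v 2 | 2/45 = 0.044 | 17% / 51% / 84% |
| Same after losing one active subject, 7 v 2 | 2/36 = 0.056 | none at 0.05 |
| Same after losing one control, 8 v 1 | 2/9 = 0.22 | none at 0.05 |
| C v D+F and its counterparts, 8 v 10 | 2/43,758 = 0.00005 | 46% / about 96% / 100% |

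Stratifying by cohort multiplies the allocation counts. Both doses of one component, each against its own F, give 2/(45 × 45) = 0.00099. After one lost control this is 2/(45 × 9) = 0.0049, so the stratified test tolerates a dropout that the single 8 v 2 test does not.

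For group E, 0.044 counts every allocation of 8 and 2. If the permutation set is restricted to the blocks of 5 in Section 6.3 (four E and one F each, assumed), there are 5 × 5 = 25 allocations and the smallest p is 2/25 = 0.08.

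**The case against.** The strongest defence is the study's purpose. Safety is primary, the secondary objective is to determine the immune response and not to show superiority over F, and Section 10.5 says the study is not powered for immunogenicity differences between regimens. Comparing doses across cohorts is inherent in dose escalation, and the staggered starts follow in Section 3 itself. F is summarised at every time point beside the active groups, and the safety regressions test for differences between groups. All of this stands and lowers the severity. It does not explain why the tests that are specified omit the control and use only non-randomised contrasts.

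Several stronger readings are tempting but not supported:

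- *The trial itself cannot show a response.* The design contains randomised contrasts (A, B and F together; C, D and F together; E and F), and the data for them are collected. Only the planned tests fall short.
- *Testing each active group against all six F subjects is the randomised contrast, with good power.* The 8 v 6 comparison has about 89% power at 2 SD. But four of the six controls come from other cohorts, the same weakness as in the planned tests. The own-cohort comparison is 8 v 2, with about 51%.
- *Cohort is aliased with assay run.* The Flow Chart places the interim analyses by cohort (study weeks 16, 22 and 36), which makes separate runs plausible. No section describes assay batching or says that final values come from the interim runs.
- *Lack of baseline adjustment is a serious loss.* This depends on reading the tested measures in item c as excluding the ratios in item b. Section 4.3 excludes past malaria and recent or planned exposure, so malaria-antigen baselines should be low. At an assumed baseline correlation of 0.2, the log ratio has 2 × (1 − 0.2) = 1.6 times the variance of the raw log value. Adjustment matters more for the influenza and T-cell assays.

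**Conclusion.** The point holds for the tests as planned. All four named immunogenicity contrasts are between separately randomised cohorts. None uses F, against the role Section 3 gives it. The tests cannot establish from a randomised contrast that PEV 301 or PEV 302 induces a response. Their dose and combination findings are open to cohort differences: about 15% or 44% false rejection under an assumed shift of 0.5 or 1 SD, against about 5% with none.

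The contrasts and the allocation come straight from the text. The rejection rates and powers rest on assumed normal log values and shift sizes, since the protocol gives neither. The 8 v 10 contrast also needs the other antigen to be a valid negative control. The severity is should-fix.

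**What to change.** In Section 10.6c, and in the matching Synopsis text:

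1. For each antigen-specific measure, add exact tests within cohort: A versus B+F and C versus D+F for PEV 301, B versus A+F and D versus C+F for PEV 302. State the condition that the other antigen is a valid negative control. For cellular assays only the C/D/F tests apply.
2. Add a cohort-stratified exact test of active versus F. State that E versus its own F is 8 v 2, that its smallest p of 0.044 is lost after one dropout, and that it is mainly descriptive. Present any comparison with pooled F as supportive and partly non-concurrent.
3. Label A-C, B-D, E-C and E-D as non-randomised, exploratory comparisons.
4. Optionally, use log baseline as a covariate for assays with real baseline signal (influenza, T-cell).

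In Section 3, state that randomisation is within cohort.

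The cost is a change of wording. No new subjects, visits or assays are needed. The downside is a few more exploratory tests and more cautious conclusions on dose and combination.

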## **10.7 Final analysis**

The final analysis will be performed after evaluation of the data of the 3rd vaccination of groups E and F.

### **10.7.1 Safety evaluation**

Safety of the injected study materials will be determined as the incidence of adverse events and the occurrence of significant clinical, hematological and biochemical abnormalities during the procedure and at the intervals indicated in the schedule of assessments. Listings will be made of the safety data collected at each time point.

No serious adverse events attributable to either vaccine are expected.

### **10.7.2 Immunogenicity evaluation**

The criteria for the evaluation of immunogenicity of PEV 301 and PEV 302 will be the result of the following assays:

- ELISA for antibody titers against PEV 301 and PEV 302, performed by Pevion Biotech Ltd.
- Western Blotting and IFA for antibody titers crossreactive with *P. falciparum* parasites (blood stages and sporozoites, respectively), performed by STI

In addition, the following evaluations will be made:

- T-cell proliferation assays, performed at STI
- Parasite growth/invasion inhibition assays, performed at STI
- Isotyping, performed at STI
- ELISPOT and clonal T-cell analyses, performed at STI
- Influenza ELISA/HIT, performed at Pevion Biotech Ltd.

## **10.8 Interim analysis**

An interim analysis will be performed after obtaining the results following the second injection of vaccine. Data will be collected in study week 13 (visit 9). If no immune response or a response considered being sufficient are seen in one of the study groups after 2 vaccinations, the study for this group will be terminated, i.e. no 3rd vaccination will be given.

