| INTERIM REPORT                             | 
An interim analysis will be performed after obtaining the results following the second injection of vaccine. Data will be collected in study weeks 12-14 (visit 9). If no humoral or cell mediated immune response is seen or the response considered sufficient in one of the study groups after 2 vaccinations, the study for this group will be terminated, i.e. no 3rd vaccination will be given.
                                                                                                                                                                                                                                                                                                                                                                                                                                                                                                                                                                                                                                                                                                                                                                                                                                                                                                                                                                                                                                                                                                                                                                                                                                                                                                                                                                                                                                                                                                                                                                                                                                                                                                                                                                                                                                                                                                                                                                                                                                                                                                                                                                                                                                                                                                                                                                                                                                                                                                                                                                                                                                                                                |                     |                                                                                                                                                          |                 |                                          |

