### 5.2.2 Vaccinations

Volunteers will be vaccinated on days 1, 64 (57 – 66) and 183 (176 – 187) respectively. The 3rd vaccination will not be applied, if 3 weeks after the 2nd vaccination no immune response is seen.

Prior to the vaccination the baseline AE rate has to be assessed by the investigator.

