## 8.2 Surveillance period for occurrence of adverse events

All adverse events occurring within one month (minimum 30 days) following administration of each dose of vaccine/ placebo must be recorded on the Adverse Event Form in the subject's CRF, irrespective of severity or whether or not they are considered vaccination-related.

Additionally, all serious adverse events brought to the attention of the investigator during the period starting from the day of performance of the first study procedure for each subject and ending not earlier than six months (minimum 180 days) following administration of the last dose of study vaccine for that subject must be recorded. See 8.8 for instructions for recording and reporting of serious adverse events.

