#### Safety data:

Listings will be made of the safety data collected at each time point.

Descriptive statistics will be used to analyze adverse events (AEs) including intercurrent illnesses. The number of AEs and their severity will be reported using frequency tables. With frequently occurring (10 or more) event types, effects of dose and vaccine will be tested by

recording the presence/absence of the event in each patient and using logistic regression models to test for differences between groups.

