## 10.9 Criteria for exclusion from analysis

Safety data analysis will be performed on all subjects who received at least one dose of study vaccine/virosomes, and for whom at least one set of safety follow-up data is available (i.e. safety population).

Subjects will be included in the final analysis of immunogenicity if they fulfill the following criteria (i.e. per protocol analysis):

- All inclusion/exclusion criteria were respected
- They received the vaccine they were randomized to receive
- They received a second dose of the vaccine
- Allowed intervals between injections were respected
- Allowed intervals between blood sampling schedules were respected
- No forbidden vaccine or concomitant medication was taken

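### The protocol gives two different rules for withholding dose 3; separately, under any version of the rule, the per-patient adverse event test in 10.6 favours a group stopped at two doses

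*Protocol*

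**What the plan says.** **The dose-3 rule.** Section 3 of the protocol sets the default: "Study participants will be vaccinated three times". It then gives one exception, which begins "If any of the study groups does not show any immune response 3 weeks after the" and refers to the second vaccination. Section 5.2.2, the operational section on vaccinations, has the same single exception: dose 3 is not given if three weeks after the second "vaccination no immune response is seen".

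The synopsis (interim report) has two grounds: "If no humoral or cell mediated immune response is seen or the response considered sufficient in one of the study groups after 2 vaccinations". Section 10.8 has the same two in slightly different words: "If no immune response or a response considered being sufficient are seen in one of the study groups after 2 vaccinations". In each of these places except 5.2.2, which does not name the unit, the rule is stated for a whole study group.

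**The safety comparison.** For event types that occur 10 or more times, Section 10.6 tests effects of dose and vaccine by "recording the presence/absence of the event in each patient and using logistic regression models to test for differences between groups". Section 10.9 defines who is included: "Safety data analysis will be performed on all subjects who received at least one dose of study vaccine/virosomes", provided some safety follow-up exists. Section 8.2 sets the collection window: "All adverse events occurring within one month (minimum 30 days) following administration of each dose of vaccine/ placebo must be recorded". Section 10.5 says the study is not powered for differences between regimens.

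**The concern.** There are two problems, and they are separate.

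1. **Dosing.** A group that responds well after two injections gets a third under Sections 3 and 5.2.2, and does not under the synopsis and 10.8 if its response is judged sufficient. This is a first-in-human product given to healthy volunteers. Whether to inject is a protocol instruction and cannot be left to an analysis plan.

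2. **Analysis.** Safety is the primary objective. If one group ends at two doses and its comparator at three, an ever/never score gives the comparator one more chance to record an event. The stopped group then looks safer at the same risk per dose. For instance, if PEV 301 10 µg stops and PEV 301 50 µg continues, the tested dose effect is mixed with the number of injections.

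**Working it through.** **The rule, side by side**

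| Place | Dose 3 withheld if no response | Dose 3 withheld if response sufficient |
|---|---|---|
| Synopsis, interim report | yes | yes |
| Section 3 | yes | not mentioned |
| Section 5.2.2 | yes | not mentioned |
| Section 10.8 | yes | yes |

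The left column is common to all four places. It can stop one group and not another without any help from the right column, so harmonising the wording would not by itself remove the analysis problem.

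**Inputs.** Enrolment reproduces: 5 × 8 + 6 = 46, and by cohort 18 + 18 + 10 = 46. No power or significance level is stated. Group size is 8. The required recording window is at least 2 × 30 = 60 days per volunteer after two doses and 3 × 30 = 90 after three, or 480 v 720 volunteer-days in a group of 8. The protocol gives no per-dose event risk, so p = 10%, 30% and 50% are assumptions, equal in both groups.

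**Independent doses.** P(at least one event) = 1 − (1 − p)^k for k doses.

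| p | two doses | three doses | expected of 8 | odds ratio |
|---|---|---|---|---|
| 0.10 | 0.190 | 0.271 | 1.5 v 2.2 | 1.58 |
| 0.30 | 0.510 | 0.657 | 4.1 v 5.3 | 1.84 |
| 0.50 | 0.750 | 0.875 | 6.0 v 7.0 | 2.33 |

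Example at p = 0.30: (0.657/0.343) / (0.510/0.490) = 1.84.

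**Correlated doses.** If the same volunteers tend to react each time (beta-binomial), the odds ratios at p = 0.10, 0.30 and 0.50 are:

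- correlation 0.3: 1.35, 1.43, 1.55
- correlation 0.6: 1.19, 1.21, 1.24
- correlation 1: 1.00 throughout

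**Dose tested across both antigens.** Suppose A + B is compared with C + D and only one 10 µg group stops. The low-dose rate is then the average of the two- and three-dose rates. At p = 0.30 with independent doses it is (0.510 + 0.657)/2 = 0.5835, and the odds ratio is (0.657/0.343) / (0.5835/0.4165) = 1.37. At p = 0.10 and 0.50 it is 1.24 and 1.62.

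**What 8 v 8 would show at p = 0.30 (exact enumeration)**

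| Doses | stopped group has fewer affected | tie | more |
|---|---|---|---|
| independent | 64% | 17% | 19% |
| correlation 0.6 | 48% | 20% | 33% |
| correlation 1 (no bias) | 39% | 22% | 39% |

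**Chance of p < 0.05, likelihood-ratio test, at p = 0.10, 0.30, 0.50**

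- 8 v 8, independent: 10.1%, 13.3%, 12.9% with unequal doses, against 7.4%, 8.0%, 8.2% if both groups have two doses (8.2%, 8.1%, 4.7% if both have three).
- 8 v 8, correlation 0.6: 6.0%, 8.5%, 8.7%, against 5.3%, 8.0%, 8.0% with both at two doses, a rise of under one percentage point.
- 16 v 16 across antigens, independent: 6.9%, 7.3%, 10.6%, against 6.0%, 5.5%, 8.3% with all groups at three doses.

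**The case against.** **Sections 3 and 5.2.2 may just be incomplete.** Neither says *only if*, and the synopsis also sets out three injections beside its two-ground rule. That is a fair reading, and it makes the repair easy. It does not remove the conflict: each of the two sections pairs three vaccinations with one named exception, neither points to 10.8, and an investigator working from 5.2.2 would give the injection.

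**The contradiction does not cause the bias.** A reader might infer that the *sufficient* clause creates the unequal doses. The protocol does not support that, because the shared no-response ground can do so alone. This objection stands, and it is why the two points are kept apart.

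**10.6 does not say the score is pooled over all doses.** Correct. That is the natural reading of presence or absence per patient, given the safety set in 10.9 and a window that reopens after each dose, but it is an inference. An analysis plan could set a narrower period, and the protocol also plans interim tables after dose 2. The point therefore depends on that reading.

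**The 8 v 8 independent case is the least favourable.** Also correct. The across-antigen and correlated cases are clearly smaller. The 480 v 720 volunteer-days do not measure reaction risk either, since solicited reactions are counted only within 4 days of injection.

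**Conclusion.** Both points hold.

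The conflict in the dosing rule is plain in the current text and needs no assumption.

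The analysis point is conditional on groups ending at different dose counts and on 10.6 covering all doses. Under equal per-dose risk of 10% to 50% (assumed), the spurious odds ratio against the three-dose group is 1.6 to 2.3 with independent doses, about 1.2 at correlation 0.6, and 1 at perfect correlation. With independent doses it is about 1.2 to 1.6 if dose is tested across both antigens and one 10 µg group stops. The direction is the same whenever a third dose can produce a volunteer's first event.

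A reader might go further and conclude that the trial's safety assessment is invalid. The protocol does not support that: safety reporting is mainly descriptive, the study is declared unpowered for group differences, and the effect on test results is small. This should be fixed, but it is not a fatal flaw.

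**What to change.** **Dosing rule.** Put one identically worded sentence in the synopsis and Sections 3, 5.2.2 and 10.8. The sponsor decides whether *sufficient* stays as a ground; if it does, state the criterion, because four matching sentences without one still cannot be applied. Keep the humoral or cell-mediated wording for C, D and E; A and B have humoral assays only. Say that the rule applies to active groups A to E and that group F volunteers follow their cohort, continuing to dose 3 while any active group in it continues.

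**Section 10.6.** Add that, whenever groups differ in number of doses, adverse events are compared per dose, or from dose 1 through the 21 (+5)-day visit after dose 2 for all groups. Third-dose events are then reported descriptively. Do not set the cut at 30 days after dose 2. Section 3 ends a stopped group's study three weeks after that dose, while a continuing group is asked about events again at its dose-3 visit, so later days would be ascertained unequally. With the common cut, equal per-dose risk gives an odds ratio of 1.

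**Cost.** Four aligned sentences, a criterion if *sufficient* is kept, one line on groups and one addition to 10.6. No extra volunteers, visits or samples. The drawback of the through-dose-2 comparison is that events after the third dose are not formally tested.
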